### Examiners

Examiners will be manual therapists working at least 20 hours a week in their private practices in the Netherlands and registered by the Dutch Association for Manual Therapy or the Royal Dutch Society for Physical Therapy. From a database of those graduated from the Institute for Master Education in Musculoskeletal Therapy (SOMT: Stichting Opleidingen Musculoskeletale Therapie, Amersfoort, the Netherlands), 14 pairs of manual therapists will be invited to participate. Each pair works together in the same practice and practices will be selected based on their ability to logistically organise the study. We aim to include therapists who vary in years of clinical experience in manual therapy. Therapists will attend an information session followed by a two-hour training session in which procedures for digitally registering data are explained and practised. They will not receive additional training in history-taking, physical examination procedures, or using questionnaires. Pairs of therapists will be strictly requested not to discuss their experiences during the study with each other until their last patient has been included. Gender, age, years of clinical experience in manual therapy, highest diploma, practice setting, weekly amount of work related to spinal disorders (hours), teaching experience (yes/no), and participation in research (yes/no) will be recorded as professional characteristics from the participating therapists.

In each practice, a third colleague will function as a research assistant to coordinate the inclusion and flow of patients. Research assistants will be instructed with respect to applying the inclusion criteria, the order of assigning patients to therapists, and assuring blinding procedures.

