[71]. BI provides a quantification of the extent to which examiners disagree on the proportions of positive (or negative) indications. BI also ranges between 0 and 1, and is high when the difference between the discordant indications is high, chance agreement is consequently low, and kappa is inflated accordingly (bias)
[71]. P_pos_ and P_neg_ are the proportions of agreement on positive and negative indications, respectively, relative to the total number of positive and negative indications, respectively, from both therapists. Overall kappa (95% CI) will be calculated as a generalized chance-corrected reliability across all pairs of therapists. See Additional file
1 for formulas.

In addition, for each pair of therapists, separate 2×2 tables will be presented for judgements about the indication for PIVM assessment and for judgements about mobility, end-feel, and pain provocation obtained from PIVM assessment (four tables in total). Observed agreement, prevalence of positive decisions, PI, BI, p_pos_, p_neg_, and overall kappa (95% CI) will also be calculated. Analyses will be conducted using DAG_Stat
[72].

Kappa (95% CI) is interpreted in accordance with value labels as assigned by Landis & Koch
[73]: <0.00: poor, 0.00-0.20: slight, 0.21-0.40: fair, 0.41-0.60: moderate, 0.61-0.80: substantial, 0.81-1.00: almost perfect. We arbitrarily assume a lower bound of the 95% CI around overall kappa of 0.60 to indicate acceptable reliability.

Univariable logistic regression analysis will be performed to explore which demographic, professional, and clinical factors contributed to the reliability of therapists’ decision-making. Firstly, patients’ demographic and clinical factors at baseline will concern their gender, age, type of complaints, duration of complaints (less or more than three months), radiation, traumatic origin, comorbidity, pain intensity, and disability. Such factors are associated with variation in diagnostic accuracy
[74], but evidence in the context of reliability is lacking. Secondly, therapists’ professional factors will include their clinical experience and weekly amount of work related to spinal disorders. Weekly amount of work related to spinal disorders was positively associated with perceived importance and confidence related to the use and interpretation of PIVM assessment

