[20] and may, therefore, contribute to variation in diagnostic decision-making. In addition, other clinical factors will be explored involving PIVM assessment (indicated or not, and judgements on mobility, resistance, and pain provocation), the diagnostic conclusion (specific or non-specific neck or low-back pain), therapists’ level of certainty of their decision about the treatment indication, and the concordance between examination objectives and the use of PIVM assessment. Factors will be entered in the model as single covariates with the concordant decisions, either positive or negative, as the dependent variable. Concordant decisions will be coded as 1 while the discordant decisions will be coded 0. Therapists’ experience and work related to spinal disorders will be entered as mean scores from each pair. A p-value <0.05 indicates a statistically significant association between a factor and a concordant decision about whether or not SMT is indicated.

With a sample size of 165, a two-sided 95% CI around kappa would extend ±0.109 from the observed value of kappa, assuming a true value of kappa of 0.70, and a prevalence of positive decisions of 50%. Consequently, each pair of examiners will be asked to include 12 patients. Multiple imputation will be used to handle records with data points missing at random. If, for any reason, data on the primary outcome measure are not available or obtainable from one or both therapists, all data from this patient will be excluded from the analysis and the pair of therapists will be asked to include a new patient. Analyses will be conducted using IBM SPSS Statistics for Windows version 22.

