[15]. Therefore, we suppose that the results of this study will to a certain extent be generalisable to populations of manual therapists outside the Netherlands. We do, however, suggest that this study be replicated over different countries and concepts to account for local idiosyncrasies in clinical reasoning and decision-making. In addition, for practical reasons, we will choose pairs of manual therapists that work in the same practice. This may inflate reliability and by pairing therapists with different levels of experience, we aim to minimise this potential threat to the validity of the study.

Finally, when analysing the reliability of indicating SMT, we will not distinguish specifically between mobilisations or manipulations. Despite the disparate mechanisms of these interventions
[9,119], no evidence is available on whether one or the other, or both, should be preferred in any clinical situation. Results of randomised controlled trials have been conflicting so far
[120-123]. New research should focus on the relationship between clinical findings, the choice for either mobilisation or manipulation, and subsequent clinical outcomes.

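### Experience and spinal workload enter the concordance regression only as pair means, so an effect of unequal therapists on agreement cannot be detected

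*Protocol article*

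**What the plan says.** All references are to the protocol article.

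- **Outcome of the regression** (Statistical analysis): agreement within the pair on whether spinal manual therapy is indicated. "Concordant decisions will be coded as 1 while the discordant decisions will be coded 0".
- **Form of the model** (Statistical analysis): "Factors will be entered in the model as single covariates with the concordant decisions, either positive or negative, as the dependent variable".
- **Therapist factors** (Statistical analysis): the "professional factors will include their clinical experience and weekly amount of work related to spinal disorders".
- **Their coding** (Statistical analysis): experience and "work related to spinal disorders will be entered as mean scores from each pair". No difference, gap or therapist-specific term is listed.
- **Recruitment** (Examiners): "We aim to include therapists who vary in years of clinical experience in manual therapy". Each pair comes from one practice, and years of experience and weekly spinal hours are recorded for every therapist.
- **Pairing** (Potential limitations of this study): after conceding that pairs from the same practice may inflate reliability, the article adds that "by pairing therapists with different levels of experience, we aim to minimise this potential threat to the validity of the study".

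**The concern.** Agreement is a property of two people. Two features of the therapists could plausibly shape it: their general level (are experienced pairs more consistent?) and their dissimilarity (do a novice and a veteran decide differently?). The plan codes only the first.

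The gap matters here because the limitations section relies on it. Mixing experience within pairs can counter inflated reliability only if unequal experience affects agreement. The regression is the one planned model that could examine this, and its covariate is blind to it. If the pair mean for experience shows no association, the result says nothing about unequal experience, although a reader could easily take it as evidence that experience does not matter. This bears on the second objective, which names professional factors among those to be explored.

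**Working it through.** **1. The plan's own figure.** The only sizing figure is a 95% CI half-width of 0.109 at n = 165, kappa 0.70 and prevalence 50%.

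- Chance agreement: p_e = 0.5² + 0.5² = 0.50.
- Observed agreement: p_o = 0.50 + 0.70 × 0.50 = 0.85.
- SE = √[0.85 × 0.15 / (165 × 0.50²)] = 0.0556.
- Half-width = 1.96 × 0.0556 = 0.109.

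The figure reproduces, and the present point does not depend on it. It does give the information available to the regression: 165 × 0.15 ≈ 25 discordant decisions.

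**2. What averaging removes.** For a pair with values a and b, the planned covariate is (a + b)/2 and the gap is |a − b|.

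| Years of experience | Pair mean | Gap |
|---|---|---|
| 12 and 12 | 12 | 0 |
| 2 and 22 | 12 | 20 |
| 10 and 10 | 10 | 0 |
| 5 and 15 | 10 | 10 |
| 2 and 18 | 10 | 16 |

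Pairs with the same mean are identical to the model whatever their gap. This is algebra and needs no assumption. The same holds for weekly hours.

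**3. What that does to detection.** The article gives no experience distribution and no effect size, so these inputs are assumed: experience uniform from 1 to 25 years, independent within pairs; 14 pairs with 12 patients each; concordance of 85% at a gap of 8 years and a mean of 13 years; no other variation between pairs. Each scenario had 1,000 simulated studies, analysed by univariable logistic regression. Share reaching p<0.05:

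| True effect on concordance | Pair mean | Absolute gap |
|---|---|---|
| None | 5.2% | 4.1% |
| Gap only, odds ratio 0.61 per 10 years | 5.9% | 25% |
| Gap only, odds ratio 0.37 per 10 years | 5.0% | 70% |
| Gap only, odds ratio 0.22 per 10 years | 9.7% | 95% |
| Mean only, odds ratio 1.11 per year | 57% | 7.5% |

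The average correlation between mean and gap was about zero, so the mean does not stand in for the gap. The last row shows the reverse: the gap does not stand in for the mean. The two covariates answer different questions.

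**4. Does mixed pairing favour one covariate?** Under the same uniform assumption, requiring a minimum gap within every pair gives these average SDs across 14 pairs:

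| Minimum gap | SD of pair means | SD of absolute gap |
|---|---|---|
| None | 4.8 | 5.6 |
| 5 years | 3.8 | 4.4 |
| 10 years | 2.8 | 3.2 |

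Both shrink by about the same proportion: roughly 21% at a 5-year minimum and 42% at 10 years. Mixing pairs in this way costs both covariates spread. It is not a reason to prefer one of them.

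**The case against.** The strongest reply is that the pair mean is a legitimate covariate for a question the article does pose. The stated reason for including workload is that more spinal work went with greater perceived importance of, and confidence in, passive motion assessment. That is a hypothesis about level, and the mean fits it. No gap hypothesis is stated for the regression; mixed pairing is presented as a safeguard, not as an exposure to study. The analysis is called exploratory throughout, individual therapist characteristics are recorded, and results are tabulated pair by pair, so gaps could still be inspected descriptively. All of this stands. It is why the mean should stay and why the point is confined to a secondary analysis. It does not change the fact that the planned regression cannot see the contrast on which the limitations section relies.

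A reader might infer more than the article supports:

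- **That mixed pairing leaves the pair means almost without spread.** An SD of about 0.8 years would require matching the most with the least experienced across all 28 therapists. The Examiners section rules this out, because each pair already works in one practice and practices are chosen for logistical ability.
- **That a contrast in workload is also built in.** Deliberate mixing is stated for experience only. For workload, averaging loses the gap, but nothing says that pairs are formed to differ in it.
- **That therapists' certainty is miscoded.** No coding is stated for it, and a condensed article may leave that open.
- **That the investigators will conclude experience is irrelevant.** No such conclusion is planned. The risk lies in how a null result might be read.

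**Conclusion.** The point holds as a limited one. With within-pair agreement as the outcome and pair means as the only coding, the regression can address whether more experienced or busier pairs agree more. It cannot address whether unequal therapists agree less. That loss is exact. For experience it sits awkwardly with a design that mixes therapists on purpose because this is expected to bear on reliability; for workload the same loss occurs without that design link.

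The detection rates (5% to 10% for the mean against 25% to 95% for the gap, when only the gap matters) are illustrative. They rest on an assumed uniform distribution, assumed odds ratios, unconstrained pairing and no other variation between pairs. Deliberate mixing would narrow the spread of the gap and lower its detection rate. With 14 pairs and about 25 expected discordant decisions, either coding carries limited information. The primary kappa, its 0.60 criterion and the sample size are untouched.

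**What to change.** In the Statistical analysis section:

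1. Keep the pair mean for experience and for weekly spinal workload.
2. Add the absolute within-pair difference in years of experience as a further exploratory single covariate and, secondarily, the absolute difference in weekly spinal hours. Each enters its own univariable model, so the stated form of the analysis is unchanged.
3. State that a null result for the pair mean concerns level only and is not evidence that experience or workload does not matter.

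Both therapists' values are already collected, so no new data are needed. The cost is small but not zero: one or two more tests at p<0.05 in an already long exploratory list, each on at most 14 distinct pair values and about 25 expected discordant decisions. They should be reported as exploratory, with confidence intervals.

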## Discussion

The results of this study will provide 1) an estimate of the inter-examiner reliability among manual therapists of indicating SMT in patients with neck or low-back pain based on a multivariable diagnostic reasoning and decision-making process, as opposed to reliability of individual clinical tests, and 2) a first exploration of which demographic, professional, or clinical factors can explain variation in the reliability of therapists’ decision-making with specific attention to the contribution of PIVM assessment. We do not aim or hypothesise that reliability from a multivariable approach to clinical diagnostics will be higher than that from individual test diagnostics. Rather, we believe that such an estimate will be a more real resemblance of the reliability among therapists of making decisions in daily practice concerning the distinction between patients who are indicated for SMT and those who are not. In addition, this approach will add to the ongoing discussion of the identification of specific subgroups of patients that may be more likely to respond to SMT and we propose alternative research strategies for establishing treatment effects.

It has been recognised that treatment effects of SMT, or any other physiotherapy modality for that matter, especially in patients with low-back pain, are, on average, small which may be due to heterogeneity of patients obscuring a wide range of individual treatment responses and variation of treatment effects
[75]. Ever since the mid-nineties of the last century, identifying subgroups of patients that may benefit more from specific or targeted interventions has had the highest research priority
[76-81]. As a result, there has been a proliferation of subgrouping systems aiming to identify people with a particular pathoanatomical condition, a particular prognosis, or those that are more likely to respond favorably to treatment
[82]. Primary care clinicians themselves do not believe that low-back pain is one condition and they treat patients differently based on patterns of clinical signs and symptoms
[83]. Moreover, they classify patients predominantly based on pathoanatomy, but they show little consensus regarding these related patterns
[84]. With the aim to identify patients that may be more likely to show a positive response to spinal manipulation, clinical prediction rules have been derived to identify predictors in patients with neck and low-back pain
[44-47,50-55]. Unfortunately, systematic reviews have consistently concluded that there is, as yet, insufficient evidence to support the general application of these rules
[85-89]. Another systematic review found significant treatment effects favoring subgroup-specific SMT over a number of comparison treatments for pain and disability at short and intermediate follow-up based on low-quality trials
[90]. Foster et al.
[75] concluded that no subgrouping approaches have yet passed the tests for clinical value and robustness of evidence, and there is still a long way to go before closer matching of treatments to patient characteristics becomes a clinical reality. Indeed, two decades after the derivation of the Ottawa Ankle Rules
[91], their validation and implementation is still an ongoing research process worldwide and it can be assumed that following a similar pathway for far more complex problems such as the treatment of non-specific neck and low-back pain may be even more time-consuming.

When determining treatment effects of SMT, randomised clinical trials currently do not make use of patients’ full clinical health profile according to the domains of the ICF for targeting treatment. For instance, Cochrane Reviews consider primary studies including participants only based on their age and the presence of pain with or without radiation
[11,13,14]. The resulting heterogeneity among trial participants and the subsequent dilution of treatment effects may be deleterious to SMT as its effectiveness may be underestimated for certain groups of patients. The majority of primary studies in patients with neck pain do not apply well-defined clinical criteria to select patients for SMT and if they do, they use only one physical test, such as a mobility test or a pain provocation test, in order to diagnose neck pain from a mechanical origin
[92]. It is stated that clinical tests are not valid or reliable to allow targeting treatment in clinical trials
[84]. This is certainly true when the reliability of individual physical tests is considered
[26-30]. However, several of the increasingly popular predication rules also contain clinical variables that are unreliable, including PIVM assessment
[42,46,88]. Targeting SMT to a more homogeneous group of patients with neck or low-back pain, based on a multivariable diagnostic process resembling daily practice, may outweigh the disadvantages of the current selection procedures in randomised clinical trials.

Awaiting evidence from the further validation of prediction rules and other classification systems, our study could offer an initial step toward a faster and easier development of an alternative approach to the identification of those patients with spinal disorders that may show a better response to SMT based on a multivariable decision process. A satisfactory level of reliability is a prerequisite for incorporating such decision-making into the design of randomised clinical trials for establishing treatment effects of SMT and thereby validating the approach. When reliability (lower bound of 95% CI around kappa) exceeds 0.60 and with BI, arbitrarily, <0.10, patients with neck or low-back pain with a positive indication can be randomised to receive, for instance, either manual mobilisations or manipulations, or both, within a multimodal treatment on the one hand or multimodal treatment without mobilisations or manipulations on the other (Figure 
1A). Should reliability be below this cut-off but with p_pos_ (or p_neg_), arbitrarily, >60%, this strategy can still be used by randomising only those patients of which the indication was agreed upon by two manual therapists (Figure 
1B). P_pos_ and p_neg_ here indicate the absolute specific agreement on positive or negative indications, respectively, between therapists
[25].

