**Figure 1 F1:**
[figure not shown]
**A. Design of an RCT including patients positively indicated for SMT when lower bound of 95% CI around kappa >0.60 and BI <0.10. B**. Design of an RCT including only patients positively indicated for SMT by two examiners when kappa <0.60 but p_pos_ (or p_neg_) >60%.

With respect to our second research objective, it is important to note that empirical evidence for sources of bias and variation in reliability studies is lacking contrary to studies of diagnostic accuracy
[74,93-95]. Variation arises from differences between studies, for example, in terms of demographic and disease features of study participants, characteristics of examiners, setting, or test protocol. As such, it does not lead to biased estimates of reliability, but it can limit the applicability of study results
[94]. Knowledge of factors that explain variation in reliability may inform ways to improve reliability. For instance, examiner training and choosing a group of more heterogeneous study participants have been mentioned as improvement strategies, but both have their limitations and lack supporting evidence
[24]. Systematic reviews may reveal subgroups of participants, examiners, or tests that consistently show higher or lower reliability. In systematic reviews, between-study comparisons are conducted to search for these subgroups as sources of variation. However, these comparisons are less valid as they are hampered by the often strong clinical and methodological heterogeneity between studies
[96]. In addition, the identification of these sources of variation becomes even more troublesome when reliability is consistently low (or high) across studies. Within-study comparisons are the preferred method to explore variation in reliability. To date, very few studies have been undertaken in the field of manual therapy with this aim and method. Cook et al.
[97] investigated factors related to the large variability of forces used during passive accessory intervertebral movements and they found that examiners’ age, gender, experience, background and education, and frequency of use did not contribute to this variation. We present simple logistic regression analysis of concordant decisions as a flexible method that can easily be incorporated in any reliability study to explore and explain variation in reliability from a large number of demographic, professional, and clinical factors.

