[103-113]. Within the large variation in choices of treatment options by therapists, mobilisations and manipulations were only rarely among the most preferred options and their frequency of use ranged from 16% to 83% and from 2% to 37%, respectively. These figures were not substantially different for specific subgroups of manual therapists who reported remarkably low frequencies of use of manipulations in the cervical region
[36,114-116]. As we will consider reliability of indicating either mobilisations or manipulations, or both, we assume a 50% prevalence of positive indications. Choosing a higher or lower prevalence would have resulted in a larger required sample
[117].

In our sample of manual therapists and patients, we cannot rule out the possibility of a substantially higher (or lower) prevalence of positive indications for SMT. Because of such a skewed distribution of decisions, a distorted interpretation of kappa could then occur. Recently, kappa, as a relative measure of reliability, has been criticised because it can only provide information about the ability to distinguish between patients on a sample level
[25]. The authors suggest using the specific agreement parameters (p_pos_ and p_neg_) as absolute measures to quantify observer variation regarding a certain diagnosis or decision on an individual patient level
[25]. No single omnibus index, however, can be satisfactory for all purpose and situations
[69,70]. Therefore, we will calculate all recommended parameters from the 2×2 tables to allow full interpretation of reliability and agreement as related to the prevalence of concordant and discordant indications. We will not, however, correct kappa for prevalence effects and bias, for instance by calculating prevalence-adjusted bias-adjusted kappa, because this would generate values of reliability that no longer relate to the original situation
[117,118].

We will select pairs of manual therapists as examiners that share a common educational background. With this background from the largest institute for manual therapy education in the Netherlands, they likely form a representative sample from the Dutch population of manual therapists registered with the Dutch Association for Manual Therapy or the Royal Dutch Society for Physical Therapy. Manual therapy education in the Netherlands is strongly embedded within international concepts. In these traditional concepts, especially passive joint motion assessment takes a prominent place

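### The fallback criterion for a future trial (p_pos or p_neg above 60%) has no chance reference, so with a skewed prevalence it is expected to be met with zero reliability

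*Protocol article*

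**What the plan says.** The Discussion states that "A satisfactory level of reliability is a prerequisite for incorporating such decision-making into the design of randomised clinical trials". It then describes two routes to such a trial.

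- **Strategy A** (Figure 1A) applies under this condition: "When reliability (lower bound of 95% CI around kappa) exceeds 0.60 and with BI, arbitrarily, <0.10".
- **Strategy B** (Figure 1B) is the fallback: "Should reliability be below this cut-off but with p_pos_ (or p_neg_), arbitrarily, >60%, this strategy can still be used". It restricts randomisation to patients on whose indication two therapists agreed. The figure legend describes a trial "including only patients positively indicated for SMT by two examiners when kappa <0.60 but p_pos_ (or p_neg_) >60" per cent.

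Strategy B carries no lower limit on kappa, no condition on the bias index (BI) and no chance-expected reference value.

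The Statistical analysis section defines p_pos and p_neg; it says these measures "are the proportions of agreement on positive and negative indications, respectively, relative to the total number of positive and negative indications, respectively, from both therapists". On prevalence, the limitations section concedes: "we cannot rule out the possibility of a substantially higher (or lower) prevalence of positive indications for SMT".

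**The concern.** Kappa is corrected for chance; p_pos and p_neg are not. They move directly with the prevalence of positive decisions. A fixed 60% threshold on either one can therefore be passed because most decisions fall on the same side, without the therapists distinguishing between patients at all.

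The stake is a false go-ahead. At kappa 0, the patients judged positive by both therapists are a chance fraction p² of all patients. Requiring two positive decisions then selects nobody in particular, and the more homogeneous trial population that the Discussion hopes for is not obtained. The fallback is also least informative under skewed prevalence, which is where the article expects kappa to be hard to interpret and turns to specific agreement instead.

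A second problem is fit. High agreement on negative decisions says little about agreement on positive ones, yet as worded it can open a trial in positively indicated patients.

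**Working it through.** **Inputs.** From the Statistical analysis section: n = 165, planning kappa 0.70, planning prevalence 50%, and the definitions of p_pos and p_neg. From the Discussion and the Figure 1 legend: the 60% threshold. From the limitations section: reported use of 16% to 83% for mobilisations and 2% to 37% for manipulations.

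**1. The plan's own figure.** The article states: "With a sample size of 165, a two-sided 95% CI around kappa would extend ±0.109 from the observed value of kappa". With prevalence 0.50, chance agreement is 0.50² + 0.50² = 0.50, and observed agreement at kappa 0.70 is 0.50 + 0.70 × 0.50 = 0.85. The half-width is 1.96 × √[0.85 × 0.15 / (165 × 0.50²)] = 0.109. The stated precision is reproduced.

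**2. Specific agreement as a function of prevalence and kappa.** Let a and d be the proportions of concordant positive and negative decisions, and b and c the discordant ones. With common prevalence p and kappa κ:

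- a = p² + κp(1−p), and b = c = p(1−p)(1−κ), so 2a + b + c = 2p
- p_pos = 2a/(2a + b + c) = p + κ(1−p)
- p_neg = 2d/(2d + b + c) = (1−p) + κp

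At κ = 0 these reduce to p_pos = p and p_neg = 1−p. The population value therefore exceeds 60% with no agreement beyond chance when p > 0.60 (through p_pos) or p < 0.40 (through p_neg).

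**3. How often an observed table meets the rule.** Simulated 2×2 tables, n = 165, κ = 0, equal therapist prevalences, all patients treated as one overall table:

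| Prevalence | Expected p_pos / p_neg | Studies with p_pos or p_neg > 60% |
|---|---|---|
| 30% | 30% / 70% | 99.6% |
| 50% (planned) | 50% / 50% | about 2.5% |
| 55% | 55% / 45% | 12% |
| 60% | 60% / 40% | 49% |
| 65% | 65% / 35% | 90% |
| 70% | 70% / 30% | 99.6% |

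In the 30% row the trigger comes entirely from p_neg.

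**4. Unequal therapist proportions.** If the two therapists' positive proportions are r and s, independence gives p_pos = 2rs/(r+s), the harmonic mean.

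- r = 0.65, s = 0.55 (mean 0.60, BI 0.10): p_pos = 0.715/1.20 = 59.6%
- r = 0.66, s = 0.56 (mean 0.61, BI 0.10): p_pos = 0.7392/1.22 = 60.6%
- r = 0.90, s = 0.40 (mean 0.65, BI 0.50): p_pos = 0.72/1.30 = 55.4%

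Modest bias moves the boundary by less than one percentage point. Only a large difference between therapists breaks the result.

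**The case against.** **It is a Discussion proposal, not part of the analysis.** The wording is permissive, the thresholds are labelled arbitrary, and nothing in this study starts a trial. The study's own criterion for acceptable reliability is a lower 95% bound of overall kappa of 0.60. This stands, and it limits the severity. A reader might infer that the rule decides whether a trial goes ahead, or that the primary result is compromised; the article supports neither. Calling the threshold arbitrary, however, excuses the number 60 and not the missing chance reference.

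**All the parameters will be reported.** Kappa with its interval, prevalence, the prevalence index, BI, p_pos and p_neg will all be visible, so a kappa near 0 beside a p_pos of 70% would be noticed. That is true, but the stated rule uses only part of this information and would still permit the design.

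**The uncorrected index is a deliberate choice.** The article explains that specific agreement is an absolute measure meant for the individual patient. That is a legitimate reason to report it. The fault is using it alone, without a floor on agreement beyond chance, as a condition for proceeding.

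**The p_neg branch may have been meant differently.** The Discussion speaks of patients whose indication was agreed, so p_neg could have been intended to go with agreed negatives, and the figure itself is not available. The legend nevertheless reads "including only patients positively indicated for SMT by two examiners when kappa <0.60". The two wordings need reconciling, but they do not prove that agreement on negatives was meant to justify randomising positives.

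**Stronger readings that do not hold.** A reader might infer that the rule is met by chance whenever mean prevalence lies outside 40–60%. That holds only in expectation and for therapists with similar positive proportions; the 0.90/0.40 example is an exception, and at the planned 50% the rate is only about 2.5%. A reader might also point to kappa 0.20 at 50% prevalence, where p_pos and p_neg are both 0.50 + 0.20 × 0.50 = 60% and the rule is met in 67% of simulated studies. That shows leniency towards slight reliability, not agreement by chance alone. Nor is it an error that the fallback uses a point estimate while strategy A uses a confidence bound; a bound on p_pos would be a preference.

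**Conclusion.** The concern holds as a moderate correction to a proposed decision rule. As worded in the Discussion and the Figure 1 legend, strategy B can be endorsed with no agreement beyond chance, against the article's own prerequisite of satisfactory reliability. At 165 patients and kappa 0 the false go-ahead is rare at the planned prevalence, but near-certain at 70% or 30%, and both values lie within the range reported for mobilisations.

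The figures assume that the two therapists have similar positive proportions and decide independently, and that the criterion is read from the overall table of 165 patients. The article does not say whether the criterion applies overall or per pair. The algebra is the same in either case; the simulated rates apply only to the overall table.

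**What to change.** Change the strategy B sentence in the Discussion and the Figure 1 legend in two ways.

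1. Where the proposed trial randomises positively indicated patients, make the trigger p_pos only and remove the p_neg alternative. If a trial in agreed negatives was also intended, state it separately with p_neg as its own trigger.
2. Add a minimum for agreement beyond chance, for example a lower 95% bound of overall kappa above 0, or a higher minimum stated in advance. At kappa 0 a lower bound above 0 occurs in about 2.5% of studies, by construction of the two-sided interval, whatever the prevalence. A bound just above 0 still admits slight reliability, so the authors should decide whether that is enough. A separate requirement that p_pos exceed 2rs/(r+s) is unnecessary, because it is algebraically the same as an observed kappa above 0.

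The minimum should be fixed before the observed prevalence is known. The cost is a few words; overall kappa with its 95% CI and p_pos are already planned, and no further data are needed. The downside is that strategy B becomes somewhat harder to trigger.
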